### Statistical Analysis

For statistical analysis, a significance level of 5% will be adopted, and SPSS (version 22.0; IBM Corp) will be used. The analysis will be performed by intention to treat. The Kolmogorov-Smirnov normality test will be applied for all continuous variables to verify data distribution. To compare groups with regard to clinical and sociodemographic characteristics, the chi-square association test and the independent samples *t* test will be used. To test the interaction between groups and assessments, a 2-way, repeated measures ANOVA will be used. If an interaction is identified, simple main effects analyses will be performed, with adjustment for multiple comparisons (Bonferroni correction). To verify which factors influence adherence to the intervention (frequency of ≥70%), a univariate logistic regression analysis will be used. To check which factors influence satisfaction with the intervention, a simple linear regression analysis will be applied.

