### Outcome Measures

#### Overview

Assessments will be conducted at participants’ homes at baseline, after 16 weeks of the intervention, and at 6 weeks and 1 year post trial completion. The volunteers will be instructed to wear comfortable clothing, closed shoes, not to perform vigorous exercises the day before the assessment, and to wear hearing or visual aids if needed.

Baseline assessments include sociodemographic measures (age, sex, race, marital status, years of schooling, living alone, and income) and general health (BMI; medication use; morbidities; foot problems including dryness of skin, calluses, fissures, open ulcers, and deformities; history of falls, hospitalizations, level of physical activity measured with the Modified Baecke Questionnaire for the Elderly; general health assessed with the Self-Rated Health questionnaire; functional activities evaluated with the Lawton-Brody Scale; and risk of fracture measured with the Fracture Risk Assessment Tool—FRAX).

Primary and secondary outcomes will be reassessed after 16 weeks of the intervention and at the posttrial 6-week follow-up. In addition, after 16 weeks of the intervention, satisfaction and adherence to the intervention will also be assessed among the IG participants. Prospective falls will be collected from baseline to 1-year follow-up. The economic health assessment will be carried out for the period up to the posttrial 1-year follow-up.

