#### Primary Outcome Measure

The primary outcome is fall risk awareness and behavior change, which will be assessed using the Falls Risk Awareness Questionnaire (Brazil). A score range from 0 to 32 points and higher scores indicate greater knowledge about fall risk factors [13].

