### Power and Sample Size

For the primary outcome (fall risk awareness), the sample size was calculated using the G*Power 3.1 software, based on type of study design (2-way ANOVA), type I error of 5%, statistical power of 80%, moderate effect size (0.20), and number of groups (n=2). This revealed that a total sample size of 42 is required. Allowing for 20% dropout, we will recruit a sample size of 60 people.

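### The article promises intention to treat but names a repeated-measures ANOVA, which by default keeps only participants with every visit, so the primary comparison would default to a completers analysis

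*Protocol article*

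**What the plan says.** Four statements in the protocol article bear on this point.

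- **Population** (Statistical Analysis): "The analysis will be performed by intention to treat". No missing-data rule accompanies it.
- **Model** (Statistical Analysis): "To test the interaction between groups and assessments, a 2-way, repeated measures ANOVA will be used". The software is given as "SPSS (version 22.0; IBM Corp) will be used", without the procedure. The section also has a logistic regression for adherence and a linear regression for satisfaction. Both look for predictors among intervention participants and compare no arms, so the ANOVA is the only between-group outcome model.
- **Visits** (Outcome Measures, Overview): "Primary and secondary outcomes will be reassessed after 16 weeks of the intervention and at the posttrial 6-week follow-up". With baseline, the primary outcome (the Falls Risk Awareness Questionnaire, 0 to 32) has three visits. The general schedule lists a fourth, at 1 year.
- **Dropout** (Power and Sample Size): 42 participants are required, and "Allowing for 20% dropout, we will recruit a sample size of 60 people".

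**The concern.** Classical repeated-measures ANOVA, as in the SPSS GLM Repeated Measures procedure, needs a complete row for each person. One missing visit removes the person from the whole analysis, including the visits that were observed. Someone with baseline and week-16 scores who misses only the 6-week follow-up would therefore not count in the week-16 comparison either. An intention-to-treat analysis is meant to keep participants in the arm to which they were randomised. Unless missing values are filled in or another model is used, the named method does not do that.

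At stake is the protection that randomisation gives to the primary comparison. The arms differ in burden: weekly calls, an agreed plan and encouraged exercise in one, a monthly call in the other. Loss that differs between arms and is related to outcome is therefore plausible, though the article does not establish it. If poor responders left the intervention arm, the completers' group-by-visit effect would be too large.

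**Working it through.** **1. The stated sample size.** Inputs from Power and Sample Size: effect size 0.20 (read as Cohen's f), alpha 0.05, power 0.80, k = 2 groups. Assumed, because the article does not give them: m = 3 visits, correlation rho = 0.5, epsilon = 1. For the group-by-visit interaction:

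- lambda = f² × N × m / (1 − rho); df1 = (k − 1)(m − 1); df2 = (N − k)(m − 1)
- N = 42: lambda = 0.04 × 42 × 3 / 0.5 = 10.08, df 2 and 80, power 0.803
- N = 40: lambda = 9.60, df 2 and 76, power 0.782

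So 42 is reproduced as the requirement for this ANOVA with complete data. The match depends on the assumed values: m = 3 with rho = 0.3 gives 58, and with rho = 0.7 gives 26.

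**2. Who would be deleted.** Reading the 20% as the share of participants with any missing visit:

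- deleted: 0.20 × 60 = 12
- completers: 60 − 12 = 48, which exceeds 42
- power under the assumptions of step 1: 0.858 with 48, against 0.929 with all 60

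The reading matters. If instead each of the two follow-up visits were missed independently with the same probability, complete cases would be 60 × 0.90² = 48.6 at 10%, 60 × 0.85² = 43.4 at 15%, and 60 × 0.80² = 38.4 at 20% per visit. Only the last falls below 42.

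**3. Possible bias from deletion.** The article gives no information on how dropout relates to outcome, so this step is a simulation under assumptions: 30 per arm, correlation 0.5 between visits, 20% lost in each arm, all loss after week 16, and loss probability logistic in a low week-16 score. The quantity is the bias of the complete-case difference in change from baseline to week 16.

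| Slope per SD, intervention arm | Slope per SD, control arm | Complete-case bias (SD) |
|---|---|---|
| 0 (random) | 0 (random) | about 0 |
| 0.5 | 0 | about +0.05 |
| 0.75 | 0 | +0.07 |
| 1.0 | 0 | +0.08 to +0.10 |
| 1.5 | 0 | +0.11 to +0.12 |
| 1.5 | 0.75 | about +0.05 |
| 1.5 | 1.5 | about 0 |

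With all week-16 scores the bias was about 0 in every row. That follows from the set-up: because all loss comes after week 16, every week-16 score is observed. It does not show that a mixed model removes bias when people leave before week 16.

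For an assumed true effect of 0.5 SD, +0.05 SD is 10% inflation and +0.12 SD is 24%.

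**The case against.** A reader might infer that the primary result will certainly be a completers analysis, or that the plan cannot deliver intention to treat. The article does not support that. Nowhere does it say that incomplete participants will be excluded. It names SPSS but not the procedure, SPSS also offers MIXED, and an ANOVA on imputed data would be compatible with its wording. Missing-data handling and the definition of the analysis set are commonly left to an analysis plan or full protocol, neither of which is shown. Silence on imputation is therefore not an error in itself.

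A reader might also take an inflation of about one quarter as the expected size. That is the top of an assumed range. It needs steep outcome-related loss in one arm, random loss in the other and no loss before week 16. The Discussion does mention poor compliance, but with the recommendations rather than with assessments, and it offers video and telephone assessment if needed, which could limit missed visits. Power is also kept at the stated dropout.

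These points set the strength of the finding but do not remove it. The article goes beyond leaving a detail open: it names a model, and that model in its ordinary form works against the population stated in the same section. The sample size points the same way, since recruitment is raised above 42 to allow for dropout, which treats dropouts as contributing no data. A possible sphericity correction is a routine detail and not part of this point.

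**Conclusion.** The concern holds as a conflict by default. As written, with no imputation and the classical procedure, the primary between-group comparison would rest on completers, about 48 of 60 at the stated dropout, while the article promises intention to treat. Power is not harmed if the 20% counts everyone with any missing visit. The cost is possible bias at week 16, from about 0 SD (loss random or alike in both arms) to about 0.12 SD (loss after week 16 strongly related to a low score in the intervention arm only). That range rests on the simulation's assumptions, and the documents do not show where in it this trial would lie. The point should be fixed, because it concerns the primary treatment comparison and costs little. It does not show that the planned result would be invalid.

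**What to change.** In Statistical Analysis, replace the repeated-measures ANOVA with a linear mixed model (SPSS MIXED, REML, unstructured covariance) with visit, group, group-by-visit and baseline score. State that participants are analysed as randomised with every available assessment, and define the intention-to-treat set. Keep the complete-case ANOVA as a sensitivity analysis.

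State the limits too. The mixed model is valid if data are missing at random given the observed scores. It does not remove bias from loss related to unobserved scores. With baseline as a covariate, a person with no follow-up assessment adds nothing to the treatment comparison.

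The cost is a change of wording before analysis: same software, no new data and no change to trial conduct.

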**Methods:**

Older people with a history of at least 2 falls in the last year will be divided into 2 groups. The intervention group will receive case management at home for reducing the risk of falls, including a multidimensional assessment, explanation of fall risk factors, and elaboration and monitoring of an individualized intervention plan based on the identified fall risk factors, personal preferences, and available resources. The control group will be monitored once a month. Assessments (clinical data, fall risk awareness, physical and mental factors, safety at home, feet and shoes, and risk and rate of falls) will be carried out at baseline, after 16 weeks of the intervention, and at the posttrial 6-week and 1-year follow-up. After 16 weeks of the intervention, satisfaction and adherence to the intervention will also be assessed. Economic health will be evaluated for the period up to the posttrial 1-year follow-up.

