## Discussion

The MAGIC trial aims to provide rigorous direct evidence about the effectiveness and cost-effectiveness of a home-based multifactorial program targeting fall risk factors among people aged 60 years and over who have fallen at least twice in the past 12 months. We hypothesize that the IG presents better awareness of fall risk and positive behavior change in reducing fall risk factors identified by case management, thus decreasing new episodes of falls with an increasing volume of physical activity after the 16-week intervention compared to the CG; in addition, we expect that community older people in the IG will continue to show the positive results obtained after the 6-week follow-up compared to the CG.

The strengths of this MAGIC study are the follow-up of individualized case management that offers greater attention to the older people in the home environment and includes the family or caregiver in the action plan for behavior change in order to reduce the identified risk factors for falls. In addition, the program offers monitoring of the older people by a physical therapist to implement a protocol for safe physical activities at home.

The researchers may encounter some limitations during this randomized controlled trial, including difficulties in recruitment, restrictions on home visits owing to the COVID-19 pandemic, and poor compliance with the recommendations proposed by the case managers. If needed, potential solutions will be the use of remote assessments by video and telephone calls and the inclusion of additional recruitment sites.

The findings of this study may provide reliable and valuable information about the effectiveness of case management for increasing fall risk awareness and reducing fall risk in older people. This study protocol detailed the design and methodology of the research to support the transparency of results. This may also assist the design of future studies.

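### The primary outcome is tested only through a gated group-by-assessment interaction, with no primary time point and conflicting visit counts; a baseline-adjusted 16-week contrast would be clearer and usually more powerful

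*Protocol article*

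**What the plan says.** **Outcome.** Under Primary Outcome Measure: "The primary outcome is fall risk awareness and behavior change, which will be assessed using the Falls Risk Awareness Questionnaire (Brazil"). The section names a 0 to 32 scale but no visit at which the groups are to be compared.

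**Test.** Under Statistical Analysis: "To test the interaction between groups and assessments, a 2-way, repeated measures ANOVA will be used". Then: "If an interaction is identified, simple main effects analyses will be performed, with adjustment for multiple comparisons (Bonferroni correction"). No other between-group test of outcomes after baseline is given, and baseline enters as one of the repeated assessments.

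**Hypothesis.** The Discussion expects better awareness in the intervention group "after the 16-week intervention compared to the CG", and adds that the benefit should still be seen at the 6-week follow-up.

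**Visits.** The article gives two schedules:
- Four visits: the Abstract (Methods) says that assessments, in a list that includes fall risk awareness, "will be carried out at baseline, after 16 weeks of the intervention, and at the posttrial 6-week and 1-year follow-up". The first paragraph of the Outcome Measures Overview gives the same four.
- Three visits with baseline: the third paragraph of that Overview says "Primary and secondary outcomes will be reassessed after 16 weeks of the intervention and at the posttrial 6-week follow-up". It then ties the 1-year period to falls and the economic assessment.

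**Sample size.** Power and Sample Size uses "type I error of 5%, statistical power of 80%, moderate effect size (0.20), and number of groups (n=2"), giving 42, with 60 to be recruited. It states neither the number of measurements nor the correlation between them.

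**The concern.** The interaction test asks whether the difference between groups varies across the visits in any way. The Discussion asks something narrower: are the groups different at 16 weeks, and does that last? A significant interaction does not answer this by itself. A 16-week statement needs a second test, which is opened only if the first succeeds.

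Two features cost power for that statement. Baseline is treated as an outcome level rather than a covariate, so the precision gained by adjusting for it is given up. The two-step route then requires both the interaction and the simple effect to be significant.

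Separately, because the visits conflict, the primary test is not fully determined. It has 2 numerator degrees of freedom with three visits and 3 with four.

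**Working it through.** **Inputs.** From the article: alpha 0.05, power 0.80, effect size 0.20, two groups, 1:1 allocation, N = 42, 60 recruited, 20% dropout (60 × 0.80 = 48 completers). Assumed, because not stated: 0.20 is Cohen's f; correlation r = 0.5 between visits, range 0.3 to 0.7; sphericity.

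**Step 1: reproduce 42.** For the interaction with k = 2 groups and m visits, λ = f²·N·m/(1−r), df1 = m−1, df2 = (N−2)(m−1). With f = 0.20, m = 3, r = 0.5, N = 42: λ = 0.04 × 42 × 3/0.5 = 10.08, df 2 and 80, power 0.803. So 42 reproduces. With m = 4 and r = 0.5 the answer is 36.

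**Step 2: put f on the 16-week scale.** Let the group difference be 0 at baseline and d at both later visits. Its variance over the three visits is (2/9)d², and f² is a quarter of that, d²/18. Hence d = 0.20 × √18 = 0.849 SD.

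**Step 3: baseline-adjusted comparison at 16 weeks.** SE = √[(1−r²)·4/N], df = N−3, noncentral t. For N = 42, r = 0.5: SE = √(0.75 × 4/42) = 0.267, noncentrality 0.849/0.267 = 3.17, power 0.87. For N = 48: SE = 0.250, noncentrality 3.39, power 0.91.

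| N | r | Interaction, 3 visits | ANCOVA at 16 weeks |
|---|---|---|---|
| 42 | 0.3 | 0.65 | 0.80 |
| 42 | 0.5 | 0.80 | 0.87 |
| 42 | 0.7 | 0.96 | 0.96 |
| 48 | 0.3 | 0.72 | 0.85 |
| 48 | 0.5 | 0.86 | 0.91 |
| 48 | 0.7 | 0.98 | 0.98 |

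If the effect halves by the 6-week follow-up (0, d, d/2), the interaction at N = 42 and r = 0.5 falls to 0.67. The 16-week ANCOVA stays at 0.87.

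**Step 4: the full planned route to a 16-week conclusion.** This was simulated with N = 42, r = 0.5 and pattern (0, d, d). The interaction had to be significant, and then the week-16 comparison without baseline adjustment. Power is about 0.64 if that comparison is tested at 5%, and 0.51 to 0.52 with Bonferroni over three visits. At N = 48 the figures are 0.72 and 0.60, against 0.91 for ANCOVA.

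**Step 5: do the extra degrees of freedom matter?** With 48 completers, r = 0.5 and an illustrative 0.5 SD effect held at every follow-up, interaction power is 0.396, 0.404 and 0.390 for two, three and four visits. ANCOVA has 0.50. The number of visits hardly moves power, because each visit at which the effect is maintained also adds noncentrality. The gap comes from the handling of baseline.

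**Step 6: where the comparison reverses.** At f = 0.20, N = 42, r = 0.5, if the effect grows after the programme ends, the 16-week ANCOVA has power 0.43 for (0, d/2, d) and 0.73 for (0, 0.75d, d). The interaction has 0.80 in both cases.

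**The case against.** The planned analysis is a recognised and valid one under randomisation. It matches the ANOVA named in the sample size section, and the Discussion's hypothesis covers two time points, for which an interaction followed by adjusted simple effects is a reasonable approach. On the interaction test alone the loss is modest at r = 0.5 and absent at r = 0.7, and recruiting 60 adds a cushion: 42/(1−0.20) = 53 would have allowed for the stated dropout. If the effect grows after week 16, the interaction is the stronger test. All of this stands, so the point is about focus and efficiency, not validity.

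On the visits, the third paragraph of the Overview is the only text specific to primary and secondary outcomes. The Abstract's list is condensed and also covers falls, so three visits is a tenable reading. The conflict remains, because the Overview's own first paragraph gives four.

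Some stronger readings are tempting but not supported:
- **Extra degrees of freedom drain the power.** Step 5 shows that they do not.
- **An effect at a later visit alone would count as success.** The interaction can indeed be significant in that case: with 0.85 SD at the last visit only and 48 completers, it was in 86% of simulated runs. But the article nowhere defines success as a significant interaction, and the simple effects would show which visit is responsible.
- **The figure of 42 proves that three visits were planned, or is wrong.** It reproduces with three visits at r = 0.5, but two visits at r = 0.6 or four at about 0.42 also give it.

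**Conclusion.** The point holds in this form. The article fixes a test that does not directly answer its own 16-week hypothesis, names no primary time point, and contradicts itself on the visits for the primary outcome. A separate analysis plan might name a time point, but the conflict over visits lies in the article itself.

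At the planned effect the interaction gives up about 7 percentage points of power at N = 42 and about 6 at N = 48 (r = 0.5). The loss is about 14 at N = 48 for r = 0.3, and none for r = 0.7. The two-step route costs far more: about 0.64, or 0.51 to 0.52 with Bonferroni, against 0.87 at N = 42. At r = 0.5 this is below the planned 80% for a 16-week conclusion, even with 48 completers.

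These sizes rest on reading 0.20 as Cohen's f, three visits, an effect maintained as the Discussion expects, sphericity, and a correlation that the article does not state. The change should be made, but the planned test is not invalid and the sample size is not shown to be wrong.

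**What to change.** Before group comparisons are seen, and in a dated amendment or the analysis plan:

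1. Name the between-group difference in awareness score at 16 weeks, adjusted for the baseline score, as the single primary test at 5% with no interaction gate. ANCOVA or the week-16 contrast of a mixed model would serve.
2. Keep the group-by-assessment interaction and the 6-week contrast as secondary, with the 1-year contrast if awareness is measured then.
3. Reconcile the first and third paragraphs of the Outcome Measures Overview with each other and with the Abstract, so that all list the same visits for the primary outcome.

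The cost is wording. Baseline is already collected, and no extra participants or visits are needed. The price is that the pattern over time becomes a secondary result, and that power is lower than with the interaction if the effect builds up after week 16. If the team expects that, it should say so and choose the primary time point accordingly.

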### Ethics Approval, Monitoring, and Dissemination

The trial was approved by the research ethics committee of Federal University of São Carlos (CAAE: 34350620.7.0000.5504). Regarding monitoring, the researchers will be responsible for making decisions related to any need for changes to the assessment and intervention in the presence of adverse effects during the research. Data will be used only for scientific purposes with the utmost confidentiality and will not be transferred to any person or entity outside of the research team. Participant data will not be released. There will be no personal expenses or any benefits for the participant. If there is any damage resulting from the research, compensation will be guaranteed. The participant will have the right to withdraw from the study at any time, if they will, without prejudice to them. If necessary, at all stages of the study, participants will have access to the researchers for further enquiries (Figure 2).

**Figure 2 figure2:**
[figure not shown]
CONSORT flowchart 2010.

## Results

This is a protocol for a single-blind, parallel-group randomized controlled trial funded in July 2021 by Conselho Nacional de Desenvolvimento Científico e Tecnológico (CNPq), Fundação de Amparo à Pesquisa do Estado de São Paulo (FAPESP), and Coordenação de Aperfeiçoamento de Pessoal de Nível Superior (CAPES; grant code 001), Approved by Registro Brasileiro de Ensaios Clínicos (ReBEC; RBR-3t85fd), with data collection started in April 2021 and expected to end in December 2021. The number of recruited volunteers as of submission of this manuscript is 52.

